**Randomization**

Participants will be randomly assigned to one of three groups: the Control Group, the Digital Video-Based Learning Group (DVBLG), and the Traditional Educational Session Group (TESG). Each participant’s phone number will serve as their unique identifier, simplifying group allocation and follow-up communication without requiring participants to remember a specific code. To ensure a random allocation, we will use the RAND function in Microsoft Excel.

The process will be as follows:

1. Each participant’s phone number will be entered in a single column in Excel. The RAND function will generate a random number for each participant. These random numbers will then be used to sort the list of participants in ascending order, resulting in a randomized list.
2. Based on this sorted list, participants will be allocated sequentially to each of the three groups, ensuring equal distribution.
3. To facilitate communication, we will create a WhatsApp group for each team. We will use the group to invite the TESG to the educational session, send the educational video to the DVBLG, and provide them with instructions to watch it. Additionally, we will use the group to call them for the post-assessment.

This approach will ensure a transparent and unbiased randomization process, allowing us to assess intervention effectiveness across comparable groups.

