**5. Participants**

**Inclusion Criteria**:

- Farmers aged 18 years and older.
- Engaged in agricultural activities in the coastal region of Akkar.
- Actively using chemical pesticides.
- Access to WhatsApp on their own or a family member's device.

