**Participants Consent**

All participants will be fully informed about the research objectives, procedures, potential risks, and benefits before enrolling in the study. The consent process will prioritize participant autonomy and comprehension to ensure ethical standards are upheld.

Consent Procedure:

1. Information Session: Each participant will receive a clear, accessible explanation of the study objectives, design, and procedures in Arabic, detailing any potential risks and anticipated benefits, including the educational value of the intervention. Participants will be informed that their participation is voluntary, and they may withdraw from the study at any point without consequence.
2. Consent Form: Participants will receive a written consent form outlining key study details. This form will require a signature or, for illiterate participants, a fingerprint to indicate their agreement to participate. Participants can also ask questions about the study and receive clarification.
3. Confidentiality and Anonymity: Participants will be assured of strict confidentiality, and unique phone numbers will be used as identifiers to protect personal data. Only authorized research personnel will access identifiable information; all data will be anonymized in reports and publications.
4. Voluntary Participation and Withdrawal: It will be made clear that participation is entirely voluntary, with no penalty for declining or withdrawing. Participants may choose to exit the study at any time without affecting any future interactions or support provided through the study.

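### Shared WhatsApp groups, with the phone number as study identifier, show each farmer's number and arm to the other members, against the protocol's own confidentiality promise

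*Protocol*

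**What the plan says.** The Randomization part of Protocol section 4 states that each participant's "phone number will serve as their unique identifier, simplifying group allocation and follow-up communication". Step 3 of the same part then sets up the communication channel: "To facilitate communication, we will create a WhatsApp group for each team". The groups have three uses. Two are given together: "We will use the group to invite the TESG to the educational session, send the educational video to the DVBLG", with viewing instructions for the video arm. The third comes later in the trial: "Additionally, we will use the group to call them for the post-assessment". As the control arm receives no intervention, this last use is the only one that applies to it.

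The Participants Consent part of section 5 makes two commitments. On the identifier: "Participants will be assured of strict confidentiality, and unique phone numbers will be used as identifiers to protect personal data". On access: "Only authorized research personnel will access identifiable information; all data will be anonymized in reports and publications".

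The inclusion criteria also bear on the point. A farmer qualifies with "Access to WhatsApp on their own or a family member's device", so the number used need not be the farmer's own.

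The protocol does not mention individual messages, a broadcast list, hidden numbers, administrator-only posting, or a request not to discuss the questionnaire.

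**The concern.** A phone number identifies a person directly. Here it is also the key that labels the study record. Placing a whole arm in one shared group passes that key, together with the fact of participation and the arm, to people who are not research personnel. Participants are promised the reverse. The disclosure would come from following the protocol, not from a lapse in conduct.

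The second strand is about measurement. Interpretation of pictograms is a primary outcome (section 10), and section 8 tests label understanding with open-ended questions asked by a surveyor. If members can post in a group that is still active while interviews take place, a farmer already interviewed could tell others what was asked. Section 7 describes the video as self-paced and gives group discussion to the in-person session, so a shared chat could also add some discussion to the video arm that the plan does not describe.

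**Working it through.** The protocol gives no figure on this point, so the check compares text with text and adds a simple count.

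**Step 1. Is the exposed item covered by the promise?** The consent text restricts access to identifiable information to authorized research personnel. The Randomization text makes the phone number the unique identifier. The phone number therefore falls under the restriction.

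**Step 2. Who would see it?** The plan provides one group for each of three arms. Assumption: these are ordinary WhatsApp groups, in which members can see one another's numbers. The protocol neither describes nor excludes this. On that assumption the viewers include all the other farmers in the arm, who are not research personnel. Steps 1 and 2 together give the conflict.

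**Step 3. Does the identifier protect personal data?** The consent text says that "unique phone numbers will be used as identifiers to protect personal data". A phone number used as a study key links the record to a person and does not mask the link. That sentence needs correcting even if no groups are created.

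**Step 4. How many people see each number?** Inputs: 133 randomized (Exclusion Criteria, section 5) or 150 (Participants recruitment, section 5), and equal allocation to three arms (Randomization).

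| Total N | Arm sizes | Other members who see each number (arm size − 1) |
| --- | --- | --- |
| 133 | 133/3 = 44.3, so 45, 44, 44 | 44, 43, 43 |
| 150 | 150/3 = 50 each | 49 |

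Each number is thus visible to about 43 to 49 other participants, in all three arms. The count takes one distinct number per farmer. Shared family devices would lower it a little, but would also expose the number of someone who may not be in the trial.

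**Step 5. Are the groups active while outcomes are measured?** Step 3 of the Randomization process uses them for the post-assessment call. The Timeline (section 9) puts intervention and post-assessment in one window, July 22 to August 9, 2024: 10 days in July plus 9 in August, 19 days in all. Farmers interviewed early and late in that window would share a group. This shows that exchange is possible. It does not show that exchange would happen, or how much.

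**Step 6. Can an effect on the results be computed?** No. The protocol gives no rate of exchange and no within-arm correlation, so any loss of information or bias would rest wholly on an assumed value.

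**The case against.** The strongest reply separates the two strands.

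On confidentiality, the access sentence goes on to speak of anonymized reports, so it could be read as covering research data only. Nothing in the plan exposes questionnaire answers or scores. That members see one another's numbers is a property of the product and is not stated in the protocol. The in-person arm meets in one room, so its members will learn who shares their arm in any case. There is also a practical reason for the choice: farmers need not remember a code.

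These points limit the finding but do not remove it. What becomes visible is a number, trial membership and arm, not answers. Yet the consent sentence refers to identifiable information, and a phone number is that on any reading. Meeting in a room does not disclose phone numbers, and the other two arms do not meet at all under the plan. A code held by staff also spares farmers from remembering anything.

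On the peer channel, the objection largely stands. The protocol gives the groups only messages from the study to participants and does not say that members may post. Farmers come from three nearby villages and can talk without WhatsApp. All three arms have a group, and nothing shows that any leakage would differ between arms or which comparison it would affect. The trial also studies a video delivered by WhatsApp, so some conversation may belong to the intervention as delivered.

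**Conclusion.** The conflict between the Randomization and Participants Consent sections is real and should be resolved. It rests on the protocol's text and on one assumption, that the groups behave as ordinary WhatsApp groups do. On that basis every participant is affected, each number being visible to about 43 to 49 others. Administrator-only posting would limit the chat but would not hide the numbers.

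The within-arm channel is a secondary and unquantified concern. It would come on top of contact the farmers already have, and it is a reason to choose a cleaner channel when one is readily available.

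Three stronger readings are tempting and are not supported:

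- A reader might infer that the video's effect cannot be separated from peer exchange, or that the primary outcome is compromised. Open posting is not stated, and neither the size nor the direction of any bias can be shown.
- A reader might count every ordered pair within an arm and report thousands of disclosures. That multiplies the same 133 to 150 people; the useful figure is the number of co-members per person.
- A reader might say that farmers consent without being told of the groups. The consent procedure requires the study procedures to be explained and the consent form is not available here, so what they are told is unknown.

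**What to change.** 1. In step 3 of Randomization, replace the shared groups. Send the session invitation, the video with its instructions, and the post-assessment call from a study phone, either one-to-one or by a broadcast list that does not show recipients to each other.
2. Use a study code as the data key. Staff hold the link, and phone numbers stay in a separate contact file. Participants need not know or remember the code.
3. In Participants Consent, replace the statement that phone numbers protect personal data with a description of the code and the contact file, so that the access promise matches what will be done.

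The cost is protocol wording plus slightly more message handling: at most about 133 to 150 individual messages for a contact that goes to every arm, and about 44 to 50 for one that goes to a single arm. Arms, content, sample size and analysis are unchanged. Individual messages will not stop neighbours from talking, but they end the disclosure of numbers and remove a channel that the trial itself would have created.

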**5. Participants**

**Inclusion Criteria**:

- Farmers aged 18 years and older.
- Engaged in agricultural activities in the coastal region of Akkar.
- Actively using chemical pesticides.
- Access to WhatsApp on their own or a family member's device.

**Exclusion Criteria**:

- Farmers who do not meet the inclusion criteria.

A total of 133 participants will be enrolled and randomized.

**Participants Consent**

All participants will be fully informed about the research objectives, procedures, potential risks, and benefits before enrolling in the study. The consent process will prioritize participant autonomy and comprehension to ensure ethical standards are upheld.

Consent Procedure:

1. Information Session: Each participant will receive a clear, accessible explanation of the study objectives, design, and procedures in Arabic, detailing any potential risks and anticipated benefits, including the educational value of the intervention. Participants will be informed that their participation is voluntary, and they may withdraw from the study at any point without consequence.
2. Consent Form: Participants will receive a written consent form outlining key study details. This form will require a signature or, for illiterate participants, a fingerprint to indicate their agreement to participate. Participants can also ask questions about the study and receive clarification.
3. Confidentiality and Anonymity: Participants will be assured of strict confidentiality, and unique phone numbers will be used as identifiers to protect personal data. Only authorized research personnel will access identifiable information; all data will be anonymized in reports and publications.
4. Voluntary Participation and Withdrawal: It will be made clear that participation is entirely voluntary, with no penalty for declining or withdrawing. Participants may choose to exit the study at any time without affecting any future interactions or support provided through the study.

**Participants recruitment:**

Participants for this study will be recruited from a list of 418 agricultural farmers provided by the municipalities of three nearby coastal villages in the Akkar Governorate, northern Lebanon. These farmers are registered in the municipal database, making them eligible for recruitment in the study due to their involvement in agriculture within this region. Systematic sampling will be used, whereby every third farmer on the list will be contacted to determine eligibility and interest in participating.

To qualify, participants must be at least 18 years old, engaged in agricultural activities within the coastal area, actively using chemical pesticides, and have access to WhatsApp on a personal or family member's device. Farmers meeting these criteria will be informed about the study’s objectives, procedures, and voluntary nature, emphasizing confidentiality and the right to withdraw at any time. Consent will be obtained through signatures or fingerprints, depending on literacy levels. Farmers who are not eligible or choose not to participate will be replaced by the next farmer on the list, and this process will continue until the required sample size of 150 participants is reached.

**6. Sample Size Calculation**

The sample size calculation for this randomized controlled trial will be based on prior data from a cross-sectional study conducted in the same region, which found that only 4% of farmers routinely read pesticide labels before preparing pesticide mixtures. To achieve a statistically meaningful improvement with our educational intervention, we aim to detect an increase in this behavior by 25%—raising it from 4% to 29%.

Using a significance level of 0.05 and a power of 80%, we estimate that each group (Digital Video-Based Learning Group, Traditional Educational Session Group, and Control Group) will require approximately 35 participants, totaling 105 participants across the three groups. However, we plan to recruit additional participants to account for potential attrition and ensure a robust final sample. The number of these additional participants will be determined based on observed participation and retention rates during the recruitment phase, allowing us to meet our target sample size despite potential dropouts. This approach will help maintain sufficient statistical power throughout the study, even if some participants cannot complete all stages.

7. **Description of the interventions.**

This randomized controlled trial will involve three distinct groups, each receiving different levels of intervention:

1. **Control Group (CG)**
   Participants in the control group will receive no educational intervention and will serve as a baseline to compare the effects of the other interventions. This group will only participate in baseline and follow-up assessments to measure changes in knowledge, practices, and understanding of pesticide labels without external educational support.
2. **Digital Video-Based Learning Group (DVBLG)**
   The participants in this group will receive a 4-minute educational video on pesticide safety distributed via WhatsApp. The video will cover essential topics on pesticide use, focusing on reading pesticide labels, understanding FAO pictograms, interpreting color codes, and practicing safe handling procedures, including using personal protective equipment (PPE). Visual aids and examples will be incorporated into the video to enhance comprehension, and the content will be presented in Arabic to ensure clarity and accessibility. The video will be available for rewatching, allowing flexible, self-paced learning. Participants in this group will receive a transportation fee as an incentive for participating.
3. **Traditional Educational Session Group (TESG)**
   Participants in the traditional educational session group will attend an in-person, interactive training session. This session, led by the primary researcher with support from a plant protection specialist and an environmental health professor, will use PowerPoint presentations and encourage group discussions. Topics covered will mirror those in the video, including pesticide safety, label interpretation, pictograms, color coding, and PPE usage. The face-to-face format will allow for immediate questions, personalized guidance, and opportunities for farmers to share their experiences. The session will take place in the Safadi Foundation’s conference room in Der Dalloum, Akkar, with participants receiving transportation fees and breakfast as incentives.

Each intervention is designed to improve the participants' knowledge, practices, and interpretation of pesticide safety labels, with the goal of assessing which format—digital or traditional—is more effective in a resource-limited setting. The interventions are specifically crafted to address language and literacy barriers, ensuring accessible and practical education for the farmers involved.

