**10. Outcomes**

**Primary Outcome Measures**:

- Ability to correctly identify and interpret FAO pictograms on pesticide labels.
- Knowledge of health risks associated with pesticide use.
- Understanding of the environmental consequences of pesticide misuse.

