**12. Statistical Analysis**

The statistical analysis for this study will be conducted using the Statistical Package for the Social Sciences (SPSS; Chicago, IL, USA), version 25, with statistical significance set at p<0.05p < 0.05p<0.05.

Descriptive Analysis

The baseline characteristics of the participants across the three groups—Control Group (CG), Digital Video-Based Learning Group (DVBLG), and Traditional Educational Session Group (TESG)—will be summarized using descriptive statistics. For continuous variables, such as age and years of experience, we will calculate the mean and standard deviation (SD). For categorical variables, such as gender and prior pesticide training, frequencies and percentages will be presented.

Baseline Comparison

To confirm the comparability of the groups before the intervention, baseline characteristics will be assessed using a one-way analysis of variance (ANOVA) across the three groups, ensuring no significant differences could affect outcome interpretation.

Primary Outcome Analysis (Per-Protocol)

A per-protocol approach will be applied to analyze the primary outcomes, which include knowledge of pesticide safety, interpretation of pesticide labels, and understanding of the environmental impacts of pesticide misuse. The analysis will proceed as follows:

- Within-Group Changes: Paired t-tests will assess changes from baseline to post-intervention for each group.
- Between-Group Differences: A one-way ANOVA will compare differences between the groups in post-intervention scores. If significant differences are detected, post hoc tests (e.g., Tukey’s HSD) will be conducted to explore pairwise comparisons between groups.

Secondary Outcome Analysis

For secondary outcomes, including PPE usage and pesticide-handling practices, changes within each group will be assessed using paired t-tests, while differences between groups will be analyzed using one-way ANOVA with post hoc tests for further analysis as needed.

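### The 80% power at 35 per arm applies to one label-reading comparison, not to any primary outcome or to video versus in-person

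*Protocol*

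**What the plan says.** Section 6 (Sample Size Calculation) starts from an earlier cross-sectional survey in which "only 4% of farmers routinely read pesticide labels before preparing pesticide mixtures". The target is given as "we aim to detect an increase in this behavior by 25%—raising it from 4% to 29"%. The power statement opens "Using a significance level of 0.05 and a power of 80%, we estimate that each group" and, after naming the arms, concludes that each "will require approximately 35 participants, totaling 105 participants across the three groups". No test, sidedness, pair of arms or multiplicity adjustment is named, and no mean difference or SD for any score is given. Farmers beyond 105 are described as cover for attrition: "The number of these additional participants will be determined based on observed participation and retention rates during the recruitment phase". Elsewhere the protocol plans 133 participants (Exclusion Criteria) and 150 (Participants recruitment).

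Section 10 lists three primary outcomes. The first is "Ability to correctly identify and interpret FAO pictograms on pesticide labels"; the others are knowledge of health risks and understanding of environmental consequences. The secondary outcomes are awareness of the importance of protective equipment, and reported changes in handling practices and equipment compliance. Section 12 compares the arms on post-intervention scores by one-way ANOVA. If that is significant, post hoc tests, with Tukey's HSD as the example, "will be conducted to explore pairwise comparisons between groups". The Hypothesis and the primary objective concern the video against the in-person session.

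**The concern.** The sample size rests on a yes/no behaviour, while the primary analysis concerns three scores. The 4% to 29% contrast is naturally an educated arm against an uneducated one, so it carries no information about the difference between two educated arms, which is what the Hypothesis and the primary objective ask about. It also appears to allow for one comparison, where Section 12 can make three.

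This is the protocol's only power statement. A reader would take it to cover the primary outcomes and the video versus in-person comparison. If those arms did not differ significantly, the stated power could be cited as support for the video being as good, which the calculation cannot give.

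**Working it through.** **Inputs.** Section 6: proportions 0.04 and 0.29, alpha 0.05, power 0.80, 35 per arm. Randomization section: equal arms ("participants will be allocated sequentially to each of the three groups, ensuring equal distribution"). Planned totals give 105/3 = 35, 133/3 ≈ 44 and 150/3 = 50 per arm; 44 and 50 assume no dropout.

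**1. Reproducing 35.** Pooled-variance formula for two proportions, two-sided, no continuity correction:

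n = [z(0.975)·√(2p̄(1−p̄)) + z(0.80)·√(p₁(1−p₁) + p₂(1−p₂))]² / (p₂−p₁)²

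- p̄ = (0.04 + 0.29)/2 = 0.165, and 2p̄(1−p̄) = 0.27555
- p₁(1−p₁) + p₂(1−p₂) = 0.0384 + 0.2059 = 0.2443
- n = (1.960 × 0.5249 + 0.8416 × 0.4943)² / 0.25² = (1.0288 + 0.4160)² / 0.0625 = 33.4, so 34 per arm

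Power at 35: Φ[(0.25·√35 − 1.0288)/0.4943] = Φ(0.911) = 81.9%. So 35 is sound for this comparison. A one-sided version with continuity correction also gives 34, so the sidedness is inferred. A Bonferroni allowance for three pairs (alpha 0.0167) gives 44.8, so 45, which suggests that no adjustment was made.

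**2. Matching endpoint to outcomes.** Label reading before mixing is not among the three primary outcomes. It could fall under reported handling practices, a secondary outcome, but is not named there. Section 6 has no SD or difference for a score, so power for the primary outcomes cannot be derived from the document.

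**3. What the sample supports for a score.** Assume a common SD, roughly normal scores and equal arms. The Tukey critical value for a pairwise t is c = q(0.95; 3, 3n−3)/√2. The detectable difference at 80% power comes from the non-central t distribution (close to (c + 0.84)·√(2/n)). The half-width of the Tukey-adjusted 95% interval is c·√(2/n). Both are in SD units.

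| Evaluable per arm | c | √(2/n) | Difference at 80% power | Interval half-width |
|---|---|---|---|---|
| 35 | 2.378 | 0.2390 | 0.77 | 0.57 |
| 44 | 2.371 | 0.2132 | 0.69 | 0.51 |
| 50 | 2.368 | 0.2000 | 0.64 | 0.47 |

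**4. Illustration only: label reading put through Section 12.** Simulation (at least 200,000 runs per setting) of ANOVA at 0.05 followed by Tukey on the 0/1 outcome, with control at 4% and both active arms at 29%. Equal active arms follow the protocol's own hypothesis.

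| Per arm | Overall F test | One named active arm v control | Both active arms v control |
|---|---|---|---|
| 35 | 87% | 64% | 43% |
| 44 | 94% | 77% | 62% |
| 50 | 97% | 84% | 72% |

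If only one active arm works and the other stays at 4%, Tukey power for the effective arm at 35 per arm is 83%.

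**The case against.** The strongest defence is that Section 6 contains no calculation error: 35 per arm does give 80% power for 4% against 29%. That stands. The fault lies in what the figure is taken to cover.

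A reader might infer from the 64% that the planned analysis fails to deliver 80% power. The documents do not support so broad a statement. The named between-group test is the ANOVA, whose overall F test has 87% power at 35 per arm; Tukey is only an example of a follow-up; Tukey has 83% if one arm alone works; and 50 per arm reaches 84% even when both do. Moreover, Section 12 reaches label reading only if it counts as a handling practice. The 64% would also be wrong beside a proportion test, whose power depends on the test and adjustment chosen.

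A reader might also say that label reading is absent from the outcomes altogether. That is too strong, since it may sit unnamed within handling practices. Nor can power for showing that the video is as effective be computed: the protocol gives no margin, and any figure would rest on an invented one.

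The larger enrolment totals do not answer the point. Section 6 presents the extra farmers as attrition cover, and no total turns a label-reading calculation into one for scores or for video versus in-person.

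**Conclusion.** The concern holds as a mismatch. The 80% figure is correct for one unadjusted two-group comparison of label reading, and it does not apply to any of the three primary outcomes or to video versus in-person. That it refers to an active arm against control, two-sided, is an inference from the number. For the primary scores, the sample supports 80% power only for fairly large pairwise differences, about 0.64 to 0.77 SD across the sizes in the protocol. The video versus in-person difference would be estimated to within about 0.47 to 0.57 SD either way. These figures assume a common SD, near-normal scores, equal arms and Tukey's method; the SD unit is needed because the protocol gives no score SD. Whether such differences are worthwhile cannot be judged from the document, so this is not a finding that the trial is too small.

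**What to change.** In Section 6:

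- State that the 80% power at 35 per arm refers only to one unadjusted active-versus-control comparison of label reading, and give the sidedness.
- Add, for each of the three primary scores under the planned analysis, that Tukey comparisons have 80% power for a true pairwise difference of about 0.77 SD with 35 evaluable farmers per arm, 0.69 SD with 44 and 0.64 SD with 50.
- Give the expected precision for video versus in-person (Tukey-adjusted 95% half-width about 0.57, 0.51 and 0.47 SD at those sizes) and make no claim of 80% power for that contrast.

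If label reading is to be an outcome, name it in the secondary list of Section 10, specify its test, and state the power for that test. Do not carry the ANOVA and Tukey figures over to a test of proportions.

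The cost is wording. The stated power becomes less favourable; design, enrolment and data collection are unchanged.
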